# 4.0 Outcomes

This study is a pilot/feasibility study, which will be used to inform a multi-centre trial measuring the effect of transition coaching. The data required for the primary outcome includes rates of consent/recruitment, coaching session completion and data collection.

# Measurements and Measurement Instruments

Demographic data: to be collected on from chart review (by research assistant) at enrollment:

- 1. Age
  2. Sex (male, female, intersex)
  3. Gender (self-report; man, woman, non-binary, prefer not to say)
  4. Disease type
  5. Current medications
  6. Age at diagnosis
  7. Family history of rheumatic disease
  8. Comorbidities
  9. Vocation (employed/college/university/other)
  10. Estimate of household income (using postal code)
  11. Newest Vital Sign© (measure of health literacy) ^25^.

At baseline, 8-months (completion of TCI) and 11-months (3-months following TCI completion), the following will be collected:

1. Transition readiness: We will measure attitude towards transition by asking participants to what extent they agree with each of 4 statements on a five-point Likert scale ^9,26^. Readiness for transition will be assessed by asking a single question: “Do you think that you are ready to transfer to adult care?”. Responses range from 1 (“no, definitely not”) to 4 (“yes, definitely”) ^26,27^.
2. Global functional assessment: PedsQL™ 4.0 Generic Scale, validated for use in 18-25 year-olds ^28,29^, contains 15-items rated on a 5-point Likert scale (0=Never, 4=Almost always). It measures physical, emotional, social, and school functioning and is considered one of the most important measures of transition ^22,30^.
3. Disease activity: The active joint count and Physician Global Assessment (PGA) will be performed by the pediatric rheumatologist at baseline and the adult rheumatologist at their first appointment and again at follow-up for every participant. Adult rheumatologists will be blinded to assessments of the pediatric rheumatologist. The PGA is measured on a scale of 0 to 10 reflecting no disease activity to most active disease ^31^.
4. Self-efficacy: We will use the National Institutes of Health’s Patient-Reported Outcomes Measurement Information System (PROMIS®). The PROMIS® Self-Efficacy outcomes for Chronic Disease ^32,33^ evaluate the confidence of patients in performing important tasks and behaviors for managing chronic diseases, and measure one’s belief about their ability to perform behaviors to reach their health goals related to physical function, mental health and social interactions: Self-Efficacy for Managing 1) Daily Activities; 2) Emotions; 3) Managing Medications and Treatments; 4) Social Interactions; 5) Symptoms, and 6) Informational Support ^32^.

|  | Baseline | Month | | | | | | | | | | |
| --- | --- | --- | --- | --- | --- | --- | --- | --- | --- | --- | --- | --- |
|  |  | 1 | 2 | 3 | 4 | 5 | 6 | 7 | 8 | 9 | 10 | 11 |
| Recruitment | X |  |  |  |  |  |  |  |  |  |  |  |
| Demographics | X |  |  |  |  |  |  |  |  |  |  |  |
| Transition readiness | X |  |  |  |  |  |  |  | X |  |  | X |
| Global function assessment | X |  |  |  |  |  |  |  | X |  |  | X |
| Disease activity | X |  |  | X* |  |  |  |  |  |  |  | X* |
| Self-efficacy (PROMIS) | X |  |  |  |  |  |  |  | X |  |  | X |
| Physio TC Intervention |  | X† | X† | X† | X† | X† | X† |  |  |  |  |  |
| SW TC Intervention |  |  |  |  |  |  |  | X† | X† |  |  |  |
| Participant satisfaction |  |  |  |  |  |  |  |  |  |  |  | X |

* First adult rheumatologist visit will occur within 3 months of consent (last scheduled pediatric visit). Follow-up after that will be as clinically indicated. Follow-up disease activity will thus be recorded when the patients return to assessment within the 11-month period

† The order of the physiotherapist and social worker transition coach sessions is not prescribed, but the sessions will occur once a month for 8 months, for the intervention group.

Additional: coach satisfaction surveys, to be completed at the end of the study

# 5.0 Statistical Analysis

We will use frequencies (numbers and proportions) to report all feasibility outcomes related to Aim 1 including satisfaction questionnaires. Open-ended responses from participants and TCs will be used to inform modifications and refinement of the TCI for the fully powered study.

For Aim 2, descriptive statistics will summarize demographic characteristics and clinical outcomes at each time point. Baseline descriptors will also be summarized by sex and gender.

We will examine within-person, within-group and between-group changes in each PROMIS® outcome and will perform sub-analyses by sex and gender. We will determine means, medians, standard deviations and interquartile ranges as appropriate, at baseline and both follow-up times and calculate variability in changes over time. We will not perform statistical analyses of these changes or group differences as we are underpowered to detect them but will use these to calculate a sample size for a future fully powered study.

Data will be analysed using SPSS v.26 (IBM, New York, United States). Data analyses will be supervised by Drs. [name] and [name] who will support trainees in developing data analysis skills.

# 6.0 Assurance of Protocol Adherence

Completed questionnaires will be reviewed for accuracy and completeness by the research co-ordinator at the time of completion. Protocol deviations will be reviewed to correct any problems.

# 7.0 Feasibility

This primary objective of this study is to investigate the feasibility of studying this intervention and scaling it to multiple centres. A similar concept has been implemented successfully at McMaster’s Young Adult Rheumatology Clinic in March 2020 in response to the COVID-19 pandemic. An ACPAC therapist supporting an adult rheumatologist ([name]) adapted service delivery by connecting virtually with each young adult one week prior to their appointment with the adult rheumatologist. This virtual meeting created dedicated time to provide the necessary education and support required in this third stage of HCT. As this positive feedback persisted, these sessions evolved further into individualized Health Coaching Interventions (HCI), guiding the young adults to gain knowledge, skills, tools and confidence while still providing medical care and supporting the young adults psychosocial, educational, and vocational needs during these virtual sessions.

All the pediatric rheumatology staff at McMaster are investigators on this project which will allow for comprehensive recruitment of patients transitioning from pediatric to adult care. This study also is being completed in the context of previous work done by the group investigating transitional care and establishing an environment conducive to high quality transition practices through the support of the pediatric and adult rheumatology teams, a leading health care transition research team and a growing number of patient advocates interested in this initiative.

# 8.0 Generalizability

McMaster Children’s Hospital and LHSC’s Children’s hospitals are pediatric hospitals that provides care to approximately 900,000 patients ≤19 years of age in Southern/Southwestern Ontario ^34,35^. This includes both urban and rural regions, sizeable Aboriginal and immigrant communities and a broad socioeconomic demographic. As a population representative of the overall Canadian population, our results will be widely generalizable.

# Appendix A – PedQL 4.0 Generic Scales (Young Adult version)

Each question is answered on the following scale: Never a problem (0), almost never a problem (1), sometimes a problem (2), often a problem (3), almost always a problem (4)

| **Physical functioning scale** | |
| --- | --- |
| It is hard for me to walk more than one block | |
| It is hard for me to run | |
| It is hard for me to do sport activity or exercise | |
| It is hard for me to lift something heavy | |
| It is hard for me to take a bath or shower by myself | |
| It is hard for me to do chores around the house | |
| I hurt or ache | |
| I have low energy | |
|  |  |
| **Emotional functioning scale** | |
| I feel afraid or scared | |
| I feel sad or blue | |
| I feel angry |  |
| I have trouble sleeping | |
| I worry about what will happen to me | |
|  |  |
| **Social functioning scale** | |
| I have trouble getting along with other young adults | |
| Other young adults do not want to be my friend | |
| Other young adults tease me | |
| I cannot do things that others my age can do | |
| It is hard to keep up with my peers | |
|  |  |
| **Work/school functioning scale** | |
| It is hard to pay attention at work or school | |
| I forget things | |
| I have trouble keeping up with my work or studies | |
| I miss work or school because of not feeling well | |
| I miss work or school to go to the doctor or hospital | |

# Appendix B - Self-efficacy questionnaire (PROMIS)

The following questions are answered on the scale: I am not at all confident (1), I am a little confident (2), I am somewhat confident (3), I am quite confident (4), I am very confident (5)

| **Managing emotions** |
| --- |
| I can handle negative feelings |
| I can find ways to manage stress |
| I can handle upsetting situations |
| I can avoid feeling discouraged |
| I can keep emotional distress from interfering with things I want to do |
| I can bounce back from disappointment |
| I can relax my body to reduce my anxiety |
| I can handle the stress of going for treatment of my medical conditions |
|  |
| **Managing medications and treatment** |
| I can follow directions when my doctor changes my medication |
| I can take my medication when I am working or away from home |
| I can take my medication when there is a change in my usual day |
| I can manage my medications without help |
| I can remember to take my medication as prescribed |
| I can use technology to help me manage my medication and treatments |
| I can list my medications, including the doses and schedule |
| I can figure out what treatment I need when my symptoms change |
|  |
| **Managing social interactions** |
| I can talk about my health problems with someone |
| If I need help, I can find someone to take me to the doctor's office |
| I can get emotional support when I need it |
| I can ask for help when I don't understand something |
| I have someone who helps me understand medical information |
| If I need help, I have someone to help me manage my daily activities |
| I have someone to help me plan and make decisions related to my illness |
| I can communicate well with my doctors and nurses |
|  |
| **Managing symptoms** |
| I can manage my symptoms during my daily activities |
| I can manage my symptoms in a public place |
| I can work with my doctor to manage my symptoms |
| I can keep my symptoms from interfering with my personal care |
| I can manage my symptoms when I am at home |
| I can keep my symptoms from interfering with the work I need to do |
| I can find the information I need to manage my symptoms |
|  |
| **Managing daily activities** |
| I can perform my household chores |
| I can go shopping and run errands |
| I can walk around inside my house |
| I can lift and carry groceries |
| I can take care of others |
| I can manage my clothes when I need to use to the toilet |
| I can keep doing my usual activities at work |
| I can maintain a regularly exercise program |

These last questions are answered on the following scale: Never (1), rarely (2), sometimes (3), usually (4), always (5)

| **Informational support** |
| --- |
| I have someone to give me good advice about a crisis if I need it |
| I have someone to give me information if I need it |
| I get useful advice about important things in life |
| I can get helpful advice from other when dealing with a problem |
| My friends have useful information to help me with my problems |
| I have people I can turn to for help with my problems |
| Other people help me get information when I have a problem |

# APPENDIX C - Intervention Tracking Sheet

|  |  | | 1 | | 2 | 3 | | 4 | | | 5 | 6 | |
| --- | --- | --- | --- | --- | --- | --- | --- | --- | --- | --- | --- | --- | --- |
| **Pediatric to Adult Care** |  | |  | |  |  | |  | | |  |  | |
| See Doctor Alone |  | |  | |  |  | |  | | |  |  | |
| Answer questions |  | |  | |  |  | |  | | |  |  | |
| Make decisions on your own |  | |  | |  |  | |  | | |  |  | |
| Schedule your own appointments |  | |  | |  |  | |  | | |  |  | |
| Take responsibility for medications |  | |  | |  |  | |  | | |  |  | |
| Have control over health information |  | |  | |  |  | |  | | |  |  | |
| Carry health and insurance card |  | |  | |  |  | |  | | |  |  | |
| Keep own health record and immunizations |  | |  | |  |  | |  | | |  |  | |
|  |  | |  | |  |  | |  | | |  |  | |
| **Self-Advocacy** |  | |  | |  |  | |  | | |  |  | |
| Ask Questions |  | |  | |  |  | |  | | |  |  | |
| Meet with all healthcare providers alone |  | |  | |  |  | |  | | |  |  | |
| Understand privacy and confidentiality |  | |  | |  |  | |  | | |  |  | |
| Understand consent |  | |  | |  |  | |  | | |  |  | |
| Ask for what is needed |  | |  | |  |  | |  | | |  |  | |
| Able to describe disease |  | |  | |  |  | |  | | |  |  | |
| Know how to access mental health |  | |  | |  |  | |  | | |  |  | |
| Know how to advocate at school or work |  | |  | |  |  | |  | | |  |  | |
|  |  | |  | |  |  | |  | | |  |  | |
| **Medication Management** |  | |  | |  |  | |  | | |  |  | |
| Know names and doses of medications |  | |  | |  |  | |  | | |  |  | |
| Compliant with medications |  | |  | |  |  | |  | | |  |  | |
| Understand what medications are for |  | |  | |  |  | |  | | |  |  | |
| Know the side effects of medications |  | |  | |  |  | |  | | |  |  | |
| Refill medications on my own |  | |  | |  |  | |  | | |  |  | |
| Know how to contact pharmacist |  | |  | |  |  | |  | | |  |  | |
| Know how to store my medications |  | |  | |  |  | |  | | |  |  | |
| Know how to take my medications |  | |  | |  |  | |  | | |  |  | |
|  |  | |  | |  |  | |  | | |  |  | |
| **General Health** | |  | |  | | |  | |  |  | | |  |
| Carry own health card | |  | |  | | |  | |  |  | | |  |
| Book own medical appointments | |  | |  | | |  | |  |  | | |  |
| Have a family doctor | |  | |  | | |  | |  |  | | |  |
| Know all healthcare providers and how to contact | |  | |  | | |  | |  |  | | |  |
| Know my allergies | |  | |  | | |  | |  |  | | |  |
| Have a plan for medical emergency | |  | |  | | |  | |  |  | | |  |
| Contact the doctor when needed | |  | |  | | |  | |  |  | | |  |
| Understand tests, procedures and risks | |  | |  | | |  | |  |  | | |  |
|  | |  | |  | | |  | |  |  | | |  |
| **Lifestyle and Behaviours** | |  | |  | | |  | |  |  | | |  |
| Alcohol interactions with medications | |  | |  | | |  | |  |  | | |  |
| Tobacco, marijuana and drugs and medications | |  | |  | | |  | |  |  | | |  |
| Healthy eating | |  | |  | | |  | |  |  | | |  |
| Exercise | |  | |  | | |  | |  |  | | |  |
| Sleep | |  | |  | | |  | |  |  | | |  |
| Prevention or pregnancy and STD's | |  | |  | | |  | |  |  | | |  |
| Understanding pregnancy and medications/disease | |  | |  | | |  | |  |  | | |  |
|  | |  | |  | | |  | |  |  | | |  |
| **Future Planning** | |  | |  | | |  | |  |  | | |  |
| Understanding health insurance | |  | |  | | |  | |  |  | | |  |
| Traveling to medical appointments - Driver's License | |  | |  | | |  | |  |  | | |  |
| Access supports for travel if needed | |  | |  | | |  | |  |  | | |  |
| Social circles | |  | |  | | |  | |  |  | | |  |
| Relationships | |  | |  | | |  | |  |  | | |  |
| Hobbies/interests | |  | |  | | |  | |  |  | | |  |
| Education - planning, accessibility | |  | |  | | |  | |  |  | | |  |
| Vocation - planning, accessibility | |  | |  | | |  | |  |  | | |  |
| Financial planning | |  | |  | | |  | |  |  | | |  |

# Appendix D – Participant satisfaction survey

Each question will be answered on the following scale: Strong disagree, disagree, somewhat disagree, neither disagree nor agree, somewhat agree, agree, strongly agree, and have room for free text comments.

| The number of appointments was just right |
| --- |
| The length of time for each appointment was just right |
| The overall time spent (8 months) was just right |
| Topics just right - self-advocacy |
| Topics just right - medication management |
| Topics just right - general health |
| Topics just right - lifestyle and behaviour |
| Topics just right - future planning |
| Topics just right - social work topics |
| Overall, I was satisfied with the Transition Coach Intervention |
| Any other comments, any you would change? |

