# Appendix E – Transition coach satisfaction survey

Each question will be answered on the following scale: Strong disagree, disagree, somewhat disagree, neither disagree nor agree, somewhat agree, agree, strongly agree, and have room for free text comments.

| The number of appointments was just right |
| --- |
| The length of time for each appointment was just right |
| The overall time spent (8 months) was just right |
| Topics just right - self-advocacy |
| Topics just right - medication management |
| Topics just right - general health |
| Topics just right - lifestyle and behaviour |
| Topics just right - future planning |
| Topics just right - social work topics |
| Overall, I was satisfied with the Transition Coach Intervention |
| On average, how much additional time did you send on each participant outside of the virtual sessions (in hours) |
| Any other comments, any you would change? |

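### Three survey items on the amount of coaching record dissatisfaction without direction, so only voluntary comments show whether respondents wanted more or less

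*Protocol*

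**What the plan says.** Appendix D lists ten rated statements and a closing open question that invites comments and suggested changes. The response options are "Strong disagree, disagree, somewhat disagree, neither disagree nor agree, somewhat agree, agree, strongly agree, and have room for free text comments". Nine of the ten statements use the just-right wording. Three of these concern quantity: number of appointments ("The number of appointments was just right"), length of each appointment, and the overall eight-month period. Six concern topics, for example "Topics just right - self-advocacy". The tenth is "Overall, I was satisfied with the Transition Coach Intervention".

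Appendix E gives coaches the same ten statements (for example "The length of time for each appointment was just right"), an item on additional hours, and the same closing question.

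Section 5.0 (Statistical Analysis) reports the satisfaction questionnaires as numbers and proportions with the Aim 1 feasibility outcomes. It then says: "Open-ended responses from participants and TCs will be used to inform modifications and refinement of the TCI for the fully powered study". In the schedule table under Measurements and Measurement Instruments, the row "Participant satisfaction" has one entry, at month 11.

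**The concern.** Quantity can be wrong in two opposite directions, and an agreement scale on a just-right statement folds both into one. Disagreement with the number of appointments may mean that the participant wanted fewer or more. The same holds for session length (shorter or longer) and overall duration.

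This matters because the trial exists to inform a multi-centre trial (Section 4.0). The schedule of eight monthly sessions (Section 3.5) is one of the things it would hand on. If a sizeable minority is unhappy with that schedule, the planners need to know which way to move it. The planned frequency table cannot tell them, although the respondents could have.

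**Working it through.** No sample-size or power formula applies. The check is a count of items, a reading of Section 5.0, and an illustration of what the table can and cannot show.

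**1. Items affected.** Appendix D has 3 quantity items + 6 topic items = 9 just-right items. With 1 overall-satisfaction item this makes 10 rated items. Appendix E has the same ten, and its item in hours is not an agreement item. The more-or-less ambiguity is the natural reading for the 3 quantity items. For the 6 topic items, disagreement may equally mean irrelevant, poorly covered, too basic or badly timed.

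**2. Number of respondents.** Section 3.3 expects 133 × 0.85 × 0.90 = 101.7 completers, which the protocol rounds to 102. Section 3.4 allocates 1:1, so 102 / 2 = 51 coached completers. This assumes that the completion rate in Section 3.3 also applies to the month-11 contact, which the protocol does not say.

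**3. What the table shows.** The documents give no expected rate of dissatisfaction. Suppose, as an assumption, that 15 of the 51 choose one of the disagree options for number of appointments: 15 / 51 = 29%, leaving 36 (71%).

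| Truth among the 15 | Agreement scale shows | Two-sided scale shows |
| --- | --- | --- |
| all wanted fewer | 15 disagree | 15 too many, 0 too few |
| all wanted more | 15 disagree | 0 too many, 15 too few |
| split | 15 disagree | for example 8 too many, 7 too few |

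The middle column does not change, although the first two rows imply opposite changes to the programme.

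**4. What the comments recover.** Let k of the 15 write a comment that states direction. The share wanting fewer is then known only to within a band of width (15 − k) / 15, because the silent 15 − k could all lie on either side.

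- k = 0: width 15/15 = 100%
- k = 5: width 10/15 = 67%
- k = 10: width 5/15 = 33%
- k = 15: width 0

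The protocol gives no basis for predicting k, so the range is shown whole. Comments may close the gap completely or not at all, and nothing in Appendix D makes a comment compulsory.

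**The case against.** The strongest reply is that the protocol does not ask the ratings to do this work. Section 5.0 gives the ratings a descriptive role and bases refinement on the open-ended responses. The instruction in both appendices allows free text with the questions, and both forms end by asking what the respondent would change. With about 51 coached completers, every comment can be read. This stands. A reader might infer that the ratings cannot guide refinement at all, but the documents do not support that: the ratings still show which element drew disagreement, and direction is recoverable from comments.

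What the reply does not do is guarantee direction. Section 6.0 has questionnaires checked for completeness, but it does not say that an empty comment space counts as incomplete. Those who write may also differ from those who do not.

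Other stronger readings also go too far:

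- **All nine just-right items are defective.** For the six topics, disagreement is not mainly about quantity. A too-little to too-much scale could force other complaints into the wrong categories.
- **Month 11 is too late.** It is three months after coaching ends (11 − 8 = 3), but it is an existing questionnaire contact and gives a view after a period without coaching. The schedule places coaching in month 8 as well, so a month-8 survey could precede the last session. The documents give no loss rate between months 8 and 11 and no evidence of recall error.
- **Controls would be surveyed.** The satisfaction row lacks the dagger carried by the coaching rows, but that footnote is mainly about session order. The items themselves name the Transition Coach Intervention and its appointments. This is a question of labelling only.

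On Appendix E, Section 3.5 describes a physiotherapist and a social worker as coaches, so respondents appear to be very few and their comments can simply be read. The gain from rewording lies almost entirely in Appendix D.

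**Conclusion.** The point holds in a limited form. Three of the ten rated items on each survey will yield frequencies without direction, and these three describe the amount of coaching that a full trial would adopt. Direction will be known only from those who volunteer a comment, anywhere from none to all of the dissatisfied.

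The consequence is modest. Satisfaction is not one of the five feasibility criteria in Section 2.0, and no sample size or clinical outcome depends on it. The case for change is that the lost information can be obtained from every respondent at almost no cost, and cannot be reliably reconstructed afterwards. The 15-of-51 figure is illustrative. The conclusion rests on the wording of the items and the planned frequency reporting, not on that figure.

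**What to change.** In Appendices D and E, recast the three quantity items as neutral stems with a two-sided response set:

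- number of appointments: far too few, too few, about right, too many, far too many;
- length of each appointment, and overall duration: far too short, too short, about right, too long, far too long.

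Report these as frequencies, as Section 5.0 already plans, so that the proportions wanting less and more appear separately. Keep the agreement scale for the six topic items and overall satisfaction, and keep the free text and the closing question throughout.

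Optionally, label the satisfaction row in the schedule table as intervention group only, which settles the denominator. The month-11 timing is a reasonable choice and need not change.

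The cost is the rewording of three items on two forms. These items will no longer share a response format with the rest of the survey. No items or contacts are added, and the sample size, randomization and feasibility criteria are unaffected.
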